### Sample size calculation and statistics

A sample size calculation was performed with reference to a previous study that had a sensitivity of 71.0% and a specificity of 75.0% [16]. With a permissible error of 0.1 and an alpha significance level of 0.05, a sample size of 50 patients per group was enough to get satisfying statistic power.

Numerical variables will be expressed as the mean ± standard deviation (SD). Student’s *t*-test will be used to assess significant differences in the above mentioned parameters between the true tumor progression and the pseudoprogression cases. Receiver operating characteristic (ROC) analyses will determine corresponding specificity, sensitivity and cutoff points for differentiating true tumor progression from pseudoprogression based on ADC, *D*, *D**, *f*, and CBF values. Associations between *f*, *D*, and corresponding CBF and ADC will be assessed with Pearson’s correlation and partial correlation analyses, respectively. SPSS 17.0 software (SPSS Inc, Chicago, IL, USA) will be used for all statistical analyses and *p* < 0.05 indicate statistical significance.

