**Methods:**

Patients that recently received a histopathological diagnosis of GBM at our hospital are eligible for enrollment. The patients selected will receive standard concurrent chemoradiotherapy and adjuvant temozolomide after surgery, and then will undergo conventional MRI, IVIM-DWI, 3D-ASL, and contrast-enhanced MRI. The quantitative parameters, ADC, *D*, *D**, *f*, and CBF, will be estimated for newly developed enhanced lesions. Further comparisons will be made with unpaired *t*-tests to evaluate parameter performance in differentiating true progression from pseudoprogression, while receiver-operating characteristic (ROC) analyses will determine the optimal thresholds, as well as sensitivity and specificity. Finally, relationships between these parameters will be assessed with Pearson’s correlation and partial correlation analyses.

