### Primary outcome measure

 Differences in diffusion-related parameters between true tumor progression and pseudoprogression according to the different fitting model
*D* and ADC will be derived from biexponential and monoexponential models, respectively. We hypothesized that true tumor progression and pseudoprogression can be distinguished based on these two values and true tumor progression can exhibit significantly lower mean *D* and ADC values compared with pseudoprogression. In addition, we hypothesized that *D*, which separates perfusion effects, will be a more promising parameter in distinguishing true tumor progression from pseudoprogression compared with ADC which can be compromised by perfusion. Differences in perfusion-related parameters between true progression and pseudoprogression Data regarding *D**, *f*, and CBF will be summarized. We hypothesized that *D**, *f*, and CBF will significantly differ between true tumor progression and pseudoprogression and Mean D*, f, and CBF values will be signifcantly lower for pseudoprogression than for true progression. Diagnostic Performance of the IVIM and 3D-ASL Parameters Receiver operating characteristic (ROC) analyses will determine corresponding cutoff points for differentiating true tumor progression from pseudoprogression based on ADC, *D*, *D**, *f*, and CBF values. In addition, sensitivity, specificity, and area under curve (AUC) for identifying true progression will be calculated in each case when pseudoprogression is differentiated. We will make a comparison among all the IVIM and 3D-ASL parameters to identify which has the best sensitivity/specificity with regards to early diagnosis. Establishment of Clinical prediction modelSingle factor analysis will show which covariates affect the judgment of newly developed enhanced or enlarged enhanced lesions, such as age, gender, radiation dose, karnofsky performance score, lesion region and imaging characteristics. A logistic regression equation will be performed to identify those covariates, IVIM and 3D-ASL parameters that contribute to the diagnostic differentiation between true progression and pseudoprogression.

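### Each cut-off, its sensitivity and specificity, and the best of five parameters all come from the same patients, so the stated procedure yields apparent accuracy that is expected to be too high

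*Protocol article*

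**What the plan says.** The Methods part of the abstract says that ROC "analyses will determine the optimal thresholds, as well as sensitivity and specificity". The section on sample size and statistics repeats this for ADC, D, D*, f and CBF: the "analyses will determine corresponding specificity, sensitivity and cutoff points for differentiating true tumor progression from pseudoprogression". The cut-off and its accuracy are thus two outputs of one analysis.

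Under Primary outcome measure, the plan adds a choice between parameters: "We will make a comparison among all the IVIM and 3D-ASL parameters to identify which has the best sensitivity/specificity". It also builds a clinical prediction model. Single-factor analysis is applied to covariates "such as age, gender, radiation dose, karnofsky performance score, lesion region and imaging characteristics", and then "A logistic regression equation will be performed to identify those covariates, IVIM and 3D-ASL parameters that contribute to the diagnostic differentiation".

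Methods/Design describes one prospective single-institution study. The article states no cut-off fixed in advance, no held-out patients and no resampling. Accuracy and the prediction model are both listed under the primary outcome.

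**The concern.** A cut-off chosen to maximise performance in a sample fits that sample's chance features as well as the real difference between groups. Sensitivity and specificity read at that cut-off in the same sample are apparent values, and on average they exceed what the same cut-off achieves in new patients. Naming the best of five parameters on those values adds a second round of selection. A multivariable model with many candidates and few patients adds a third.

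The Discussion says that the study attempts to validate these parameters. The Background explains that mistaking pseudoprogression for true progression leads to unsuitable changes of therapy. Readers may therefore take the reported thresholds and accuracy at face value. The limitations that the article lists do not include this one.

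**Working it through.** **Inputs from the protocol article.** Sensitivity is 0.71 and specificity 0.75, from a previous study. The precision target reads "With a permissible error of 0.1 and an alpha significance level of 0.05". The planned size is 50 per group. There are five imaging parameters and at least six named covariates.

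**Step 1: the plan's own figure.** The usual precision formula is n = z² p(1 − p) / d², with d = 0.1.
- Two-sided 5%: 1.96² × 0.71 × 0.29 / 0.01 = 79.1, so 80 for sensitivity. 1.96² × 0.75 × 0.25 / 0.01 = 72.03, so 73 for specificity.
- One-sided 5%: 1.645² gives 55.7 (56) and 50.7 (51).

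The stated 50 is close only to the one-sided specificity figure. At n = 50 the two-sided half-widths are 1.96 × √(0.71 × 0.29 / 50) = 0.126 and 1.96 × √(0.75 × 0.25 / 50) = 0.120. That shortfall is a separate matter, and the present point does not depend on it. The figures serve here as a yardstick for the bias.

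**Step 2: a working truth.** With equal-variance normal data, 71%/75% corresponds to a group difference of z(0.71) + z(0.75) = 1.228 SD. The AUC is then Φ(1.228/√2) = 0.807. Taking 71%/75% as the truth is an assumption.

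**Step 3: simulate the stated procedure.** In each simulated trial of 50 per group, take the cut-off with the largest Youden index (J = sensitivity + specificity − 1) and record the apparent values there. Then compute the true values of the same cut-off from the known distributions. For five parameters, keep the one with the largest apparent J. The results are averages over several thousand trials per setting. Rows with unequal parameters use a correlation of 0.5.

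| Setting (50 per group) | Apparent sens / spec | True sens / spec | J apparent v true |
|---|---|---|---|
| One parameter, 1.23 SD | 0.78 / 0.74 | 0.74 / 0.70 | 0.52 v 0.44 |
| Best of five, all 1.23 SD, correlation 0.5 | 0.81 / 0.79 | 0.73 / 0.71 | 0.59 v 0.45 |
| Best of five, all 1.23 SD, correlation 0 | 0.81 / 0.80 | 0.73 / 0.71 | 0.61 v 0.45 |
| Best of five, 1.23, 1.0, 0.8, 0.6, 0.4 SD | 0.79 / 0.75 | 0.73 / 0.69 | 0.53 v 0.43 |
| Best of five, one 1.23 SD and four 0.6 SD | 0.78 / 0.74 | 0.74 / 0.70 | 0.52 v 0.44 |

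Half the gap in J is the average overstatement of each measure:
- one parameter: (0.52 − 0.44)/2 = 0.04
- five alike and uncorrelated: (0.61 − 0.45)/2 = 0.08
- graded effects: (0.53 − 0.43)/2 = 0.05
- one dominant parameter: (0.52 − 0.44)/2 = 0.04

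Apparent J exceeds true J in about 85% of simulated trials with one parameter, and in about 99% or more when five equal parameters compete.

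**Step 4: what is not affected.** For one parameter the mean apparent AUC is 0.809 against a true 0.807, because the AUC uses no cut-off. It rises only through selection: 0.84 to 0.85 for the best of five equal parameters. The t-tests involve no cut-off either.

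**Step 5: the prediction model.** Six named covariates plus five imaging parameters make at least 11 candidates, and 50/11 = 4.5 patients in the smaller group for each. In an illustrative simulation the five imaging parameters always entered (correlation 0.5). Six uninformative covariates were screened at p < 0.05, screened at p < 0.20, or not screened. Apparent AUC exceeded the AUC in new patients by 0.03 to 0.07 with real signal, and by 0.14 to 0.19 with none. The entry rules are assumptions, since the article gives none.

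**The case against.** The strongest reply is that this is a condensed article. The threshold rule, internal validation and the model-entry rule commonly sit in a full protocol or analysis plan, and neither is shown. A reader might infer that no correction will ever be made. The documents support only that none is stated. What remains is a matter of what the article does fix: followed as written, its primary-outcome procedure produces apparent accuracy.

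A second reply concerns size. The 8-point figure needs five equally good parameters, whereas the primary outcome section expects D to do better than ADC. That is right, and 8 points is close to a ceiling. With unequal parameters the overstatement falls to 4 or 5 points, well inside the sampling half-width of about 12 points at n = 50. But sampling error goes either way, whereas this bias is expected to go one way.

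A third reply is that the logistic regression is meant to identify contributors, and no accuracy measure is promised for it. This stands. The expectation that model accuracy will be reported comes from the heading about a clinical prediction model and from a remark in the Discussion about the combined techniques.

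Some stronger readings are tempting but lack support:
- That the sample size presumed a fixed threshold. The article only cites 71% and 75% from a study that is not at hand, and those figures may themselves come from an optimised cut-off.
- That D and ADC are nearly collinear. The secondary outcome only hypothesises a significant correlation.
- That all 11 candidates are screened at p < 0.05. Single-factor analysis is described for covariates, with no entry rule.
- That the smaller group will have only 20 to 30 patients. The plan says "a sample size of 50 patients per group was enough to get satisfying statistic power" and fixes no total of 100.

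**Conclusion.** The point holds. As stated, the plan selects each cut-off, reports accuracy at it and names the best parameter in the same patients, so its sensitivity and specificity are apparent values with an expected upward bias.

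With 50 per group, equal-variance normal data, a Youden cut-off and a true AUC of 0.81, the overstatement is about 4 points each for one parameter. For the best of five it is about 4 to 8 points each (J 0.52 to 0.61 apparent against 0.43 to 0.45 true), depending on how alike the parameters are. The upper end would use up most of the 10-point permissible error. The direction was the same in every setting tried, but the size rests on these assumptions, and a single data set could go the other way.

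Any accuracy quoted for the logistic model would be optimistic too, at about 4.5 patients in the smaller group per candidate. A reader might infer that every primary result is inflated. That goes too far: cut-off choice leaves the group comparisons by t-test and the AUC of a single pre-named parameter untouched.

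**What to change.** 1. Name the threshold rule, for example the maximum Youden index.
2. Repeat cut-off choice, best-parameter choice and model building, including any single-factor screening, inside each bootstrap sample (or each fold of a cross-validation).
3. Report optimism-corrected sensitivity, specificity and model AUC with 95% intervals as the main result, and show the uncorrected values labelled as apparent.

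No extra patients or scans are needed. The cost is a few sentences in the plan, some programming outside the standard menu analysis in SPSS, and reported accuracy a few points lower.

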### Primary outcome measure

 Differences in diffusion-related parameters between true tumor progression and pseudoprogression according to the different fitting model
*D* and ADC will be derived from biexponential and monoexponential models, respectively. We hypothesized that true tumor progression and pseudoprogression can be distinguished based on these two values and true tumor progression can exhibit significantly lower mean *D* and ADC values compared with pseudoprogression. In addition, we hypothesized that *D*, which separates perfusion effects, will be a more promising parameter in distinguishing true tumor progression from pseudoprogression compared with ADC which can be compromised by perfusion. Differences in perfusion-related parameters between true progression and pseudoprogression Data regarding *D**, *f*, and CBF will be summarized. We hypothesized that *D**, *f*, and CBF will significantly differ between true tumor progression and pseudoprogression and Mean D*, f, and CBF values will be signifcantly lower for pseudoprogression than for true progression. Diagnostic Performance of the IVIM and 3D-ASL Parameters Receiver operating characteristic (ROC) analyses will determine corresponding cutoff points for differentiating true tumor progression from pseudoprogression based on ADC, *D*, *D**, *f*, and CBF values. In addition, sensitivity, specificity, and area under curve (AUC) for identifying true progression will be calculated in each case when pseudoprogression is differentiated. We will make a comparison among all the IVIM and 3D-ASL parameters to identify which has the best sensitivity/specificity with regards to early diagnosis. Establishment of Clinical prediction modelSingle factor analysis will show which covariates affect the judgment of newly developed enhanced or enlarged enhanced lesions, such as age, gender, radiation dose, karnofsky performance score, lesion region and imaging characteristics. A logistic regression equation will be performed to identify those covariates, IVIM and 3D-ASL parameters that contribute to the diagnostic differentiation between true progression and pseudoprogression.

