There have been several studies in which researchers differentiated true progression from treatment effects by using advanced MR imaging techniques, such as diffusion weighted magnetic resonance imaging (DWI) and dynamic susceptibility-weighted contrast-enhanced (DSC) MRI. True progression exhibits significantly lower apparent diffusion coefficient (ADC) values compared with pseudoprogression [11, 12], reflecting the high cellularity of progressed tumor. Considering that ADC values can be compromised by perfusion, Le Bihan et al. introduced an intravoxel incoherent motion (IVIM) technique [13, 14]. Slow diffusion coefficient (D) is the diffusion parameter which reflects the diffusion coefficient for water while fast diffusion coefficient (D*) represents perfusion-related diffusion. Fraction of fast ADC (f) is the perfusion fraction linked to microcirculation which has been successfully applied to glioma grading and to differentiate recurrent tumors from treatment-related changes [15, 16]. DSC is a T2*-weighted technique to measure relative cerebral blood volume (rCBV) and lower mean rCBV values in pseudoprogression was previously used to differentiate from true progression [17]. However, radiotherapy and chemotherapy for GBM destroy blood–brain barrier, allowing gadolinium-based contrast agents to leak into the interstitial fluid, which may lead to the underestimation of rCBV with DSC [18]. Three-dimensional arterial spin labeling (3D-ASL) is another non-invasive and contrast agent-free perfusion imaging method to measure cerebral blood flow (CBF) [19]. The diagnostic performance of 3D-ASL has been found to be equivalent to DSC MRI in assessing brain tumor perfusion, particularly for those patients not suitable for DSC because of renal failure [20].

Despite the application of IVIM and 3D-ASL in glioma study, there still lacks study in which IVIM is combined with 3D-ASL in the same GBM patient cohort to evaluate their efficacy of differentiate true tumor progression from pseudoprogression as a consequnence of radiochemotherapy for GBM.

Therefore, the current prospective diagnostic trial was designed to evaluate the ability of IVIM-DWI and 3D-ASL to distinguish true tumor progression from pseudoprogression in GBM. The diagnostic performance of the quantitative parameters obtained from IVIM-DWI and 3D-ASL will also be compared.

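### The D-versus-ADC hypothesis and the choice of best parameter have no named test of a difference in accuracy, although all parameters are measured in the same patients

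*Protocol article*

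**What the plan says.** The Background section of the protocol article sets the comparison as an aim: "The diagnostic performance of the quantitative parameters obtained from IVIM-DWI and 3D-ASL will also be compared". The section on the primary outcome measure then makes two comparative statements. The first is that D "will be a more promising parameter in distinguishing true tumor progression from pseudoprogression compared with ADC which can be compromised by perfusion". The second is the selection step: "We will make a comparison among all the IVIM and 3D-ASL parameters to identify which has the best sensitivity/specificity with regards to early diagnosis".

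The same section describes what each ROC analysis delivers. It "analyses will determine corresponding cutoff points for differentiating true tumor progression from pseudoprogression based on" each of ADC, D, D*, f and CBF, and "sensitivity, specificity, and area under curve (AUC) for identifying true progression will be calculated in each case". It also plans a single-factor analysis and a logistic regression.

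The section on sample size and statistics names the remaining methods: Student's t-test between the two patient groups, ROC analysis by parameter, and Pearson and partial correlation, with p < 0.05 as the threshold. The abstract confirms that the t-tests are unpaired. The sample size of 50 per group is justified by a sensitivity of 71.0%, a specificity of 75.0%, a permissible error of 0.1 and an alpha of 0.05.

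**The concern.** A statement that one marker discriminates better than another is a statement about a difference in accuracy. It needs an estimate of that difference and its uncertainty. Here the markers are also paired: DWI and 3D-ASL are both scheduled for each patient's first follow-up visit, and D and ADC are fitted to the same DWI data. The uncertainty of the difference therefore depends on how strongly the markers correlate.

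The article names a method for the group differences and for the secondary correlations, but none for this comparison. What it does give is a criterion, the best sensitivity/specificity. That criterion always produces a winner, even when all parameters are equally good. The trial could then report that D is preferable to ADC, or that one technique beats the other, on a gap that chance alone would produce. The apparent accuracy of the selected parameter would be too high as well.

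**Working it through.** **1. What each named method can answer**

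| Method | Question answered | Tests D against ADC? |
|---|---|---|
| Unpaired t-test | Does one parameter's mean differ between true progression and pseudoprogression? | No |
| ROC per parameter | What are the cut-off, sensitivity, specificity and AUC of that parameter? | No: no difference, test or interval is named |
| Pearson and partial correlation | Are D and ADC, or f and CBF, associated? | No |
| Logistic regression | Which variables contribute to a joint model? | No |

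**2. The plan's own figure**

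The sample size inputs describe the precision of a single proportion, n = z²p(1−p)/e².

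- Sensitivity: 1.96² × 0.71 × 0.29 / 0.1² = 79.1, so 80.
- Specificity: 1.96² × 0.75 × 0.25 / 0.1² = 72.0, so 73.
- With a one-sided z of 1.645 the results are 56 and 51.

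The stated 50 is not reproduced for both quantities by any of these. That is a separate matter. What counts here is that no difference between parameters enters the calculation.

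**3. Simulation at 50 per group**

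Inputs: 50 per group from the article. Assumed: normally distributed markers with equal variance, a true AUC near 0.80, and the within-group correlation between markers, for which the article gives no value. There were 2,000 simulated trials per setting. The paired variance is Var(A₁−A₂) = Var(A₁) + Var(A₂) − 2Cov(A₁,A₂), estimated by the DeLong method.

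*Two equal parameters (AUC 0.80 each).* D has the higher AUC in about 49–50% of trials. The paired test declares a difference in 4–5%.

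*Sensitivity at separately optimised cut-offs.* The true AUC is set to 0.807, which corresponds to a Youden index of 0.71 + 0.75 − 1 = 0.46. Two equal parameters then differ in sensitivity by 10 points or more in 51%, 49% and 40% of trials at correlation 0.5, 0.7 and 0.9.

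*Five equal parameters.* Mean gap between the highest and lowest AUC:

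| Common correlation | 0 | 0.3 | 0.5 | 0.7 | 0.9 |
|---|---|---|---|---|---|
| Mean gap | 0.098 | 0.086 | 0.073 | 0.058 | 0.035 |

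With a true AUC of 0.807, the best of five shows an average AUC of 0.84–0.86 and an average Youden index of 0.59–0.61 (true value 0.46), at correlations of 0 to 0.6.

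*What a paired comparison can detect.*

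| Correlation of D and ADC | SE of difference (equal AUC) | Power, 0.80 vs 0.75 | Power, 0.80 vs 0.70 |
|---|---|---|---|
| 0.7 | 0.037 | 25% | 71% |
| 0.8 | 0.031 | 34% | 83% |
| 0.9 | 0.022 | 56% | 99% |

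Ignoring the pairing is costly. For a gain of 0.10 above 0.807, power is 70%, 87% and over 99% with the paired test at correlation 0.5, 0.7 and 0.9, but only 44–48% if the two AUCs are treated as independent.

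**The case against.** The strongest objection is that a journal article condenses the full protocol, and the name of a test for correlated ROC curves is a detail often left to an analysis plan. The text speaks of a comparison. It does not prescribe ranking and does not exclude a paired test. That part stands: a reader might infer that the plan commits itself to ranking point estimates, but this is an inference from the stated criterion and the list of methods. The objection does not remove the point. The article names its tests for the other hypotheses, and for this one it fixes a selection criterion that would pick a winner among equals.

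Three further limits stand.

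- AUC does not depend on a cut-off and is already planned. The objection about different operating points applies only to the sensitivity/specificity criterion. Such pairs can still be compared jointly, for example by the Youden index, though optimistically when the cut-offs come from the same data.
- A reader might expect D to be declared better because its t-test p-value is smaller. The article never says so.
- The D-versus-ADC statement is an additional hypothesis in soft terms. It sits under the primary outcome but is not worded as a formal superiority claim, and the abstract describes the purpose as exploratory.

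**Conclusion.** The concern holds in a limited form. A comparative hypothesis and a choice of best parameter stand under the primary outcome, and no method named in the article tests a difference in accuracy between parameters from the same patients. As written, the answer would come from point estimates.

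At 50 per group, that makes D against ADC close to a coin toss when the two are equal. Five equal parameters would spread by an average AUC gap of about 0.10 if uncorrelated, 0.06 at correlation 0.7 and 0.035 at 0.9. The absence of any named comparative method is read directly from the text. The sizes are illustrations that rest on normal markers, a true AUC near 0.80 and assumed correlations. The documents do not support the stronger reading that the investigators have ruled out a paired test.

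**What to change.** In the sections on statistics and on the primary outcome measure:

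1. Replace selection by best sensitivity/specificity with paired AUC differences (DeLong or paired bootstrap) and 95% intervals.
2. For the stated hypothesis, test AUC(D) minus AUC(ADC), and conclude that D is better only if the interval excludes zero in its favour.
3. Report the other pairs, including IVIM against 3D-ASL parameters, with intervals and as descriptive.
4. State that 50 per group was justified by a single sensitivity and specificity, not by a difference between parameters. Paired power is about 25–56% for an AUC difference of 0.05 and 71–99% for 0.10, at assumed correlations of 0.7 to 0.9.

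The cost is a change of wording and one routine analysis of data already being collected. The downside is that a statement that D, or any other parameter, is best may not be supported.
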